**Figure 3 Fig3:**
[figure not shown]
**Approximated patient flow of MATE-LOC.**

### Statistical analyses

All of the primary analyses will be conducted according to the intention-to-treat principle (ITT). There is a risk that not every patient in the IG will have a feedback session during his or her withdrawal treatment. This could result from time constraints for the therapists, unscheduled dropouts from treatment, or premature referrals for subsequent treatment. Therefore, additional per-protocol analyses will be conducted that include only those patients who actually participated in the intervention. In order to evaluate the robustness of the results, missing data will be addressed by using at least two procedures (e.g. complete case analyses, imputation by expectation-maximization, multiple imputation by chained equations), depending on the outcome and the patterns in the missing data. Differences between the two treatment arms regarding the primary outcomes will be analyzed using generalized linear models with gamma distribution and log-link function controlling for confounders (e.g. baseline costs and PDHD, age, gender, co-morbidity, EQ-5D scores). To account for correlated patient data caused by the multicenter structure, random-effect models will be applied.

Subgroup analyses will include effects of the classification as matched vs. mismatched decisions for patients in both the IG and the CG. That is, patients who received treatment according to MATE guidelines will be designated matched*,* and those who did not will be designated as mismatched. The effect of matching MATE recommendations with treatment received on the primary outcome measures will be analyzed using multiple linear regressions. Therapists’ documented reasons for deciding to deviate from MATE-LOC recommendations will also be analyzed in order to decide whether the decision algorithm should be modified. Additional exploratory analyses will be conducted to determine the relevance that patients’ demographic and clinical characteristics, their motivation for treatment, and their treatment preferences has for patient-treatment matching.

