### Primary outcomes

The primary outcome measures will be alcohol consumption and health-care costs; they will be assessed six months after discharge from the current withdrawal treatment. Regarding alcohol consumption, per cent days of heavy drinking in the last 30 days (PDHD) was chosen as the primary outcome measure [32]. It is derived from the MATE-Outcomes*.* Health-care costs are estimated based on data on health-service utilization as assessed with the CSSRI-EU. The estimate includes a monetary valuation with unit costs.

Outcomes for the process evaluation include quantitative and qualitative data. In addition to the assessment instruments and documentation forms used during the trial, after the data have been collected, research assistants and heads of the participating treatment wards will be invited to attend a focus group to discuss potential benefits from and barriers for an implementation of the matching guidelines.

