### Intervention

After the MATE interview with patients in the IG, the research assistant will review with the patient’s therapist or social worker, or both, the LOC recommendation based on the MATE results. In a subsequent feedback-session, the research assistant will explain the recommendation and will strive to reach a consensual decision with the patient regarding further treatment. In case a therapist has a diverging recommendation, this revised recommendation will be explained to the patient. At the end of the feedback session, the decision that the patient and research assistant have made will be documented, and the therapeutic staff will be informed about the decision.

Patients in the CG will not have an additional feedback session regarding their further treatment options and are treated as usual. These patients will receive global feedback regarding their assessment results, without a recommendation for a LOC, if they request it.

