### Procedure

Immediately after admission to the withdrawal unit, patients will be invited to take part in the study. A research assistant will inform patients about the study procedure, and patients who wish to participate will be asked to sign an informed consent. Patients who have done so will be asked to complete a questionnaire prior to their first assessment. This assessment will be scheduled when a patient’s withdrawal symptoms have decreased to a minimal level as judged by the medical staff. During the assessment interview, a research assistant will administer the MATE, CSSRI-EU, and EQ-5D. Finally, the research assistant will be informed by the computer-assisted MATE, whether the patient has been randomly assigned to either the IG or the CG. For patients in the IG, the research assistant will schedule the feedback session.

At the end of the withdrawal treatment, all decisions and arrangements regarding subsequent treatment will be documented for patients in both the IG and the CG. Six months after discharge from the withdrawal treatment, patients are contacted for a telephone follow-up interview, which will include the MATE-Outcomes, CSSRI-EU, and EQ-5D. Patients who complete the entire procedure including the follow-up assessment will receive payment of 30 euros. The study procedure is diagrammed in Figure 2.

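### The supplementary per-protocol analysis selects on an event that only intervention-arm patients can experience after randomization, so it is not a randomized comparison and its bias has no known direction

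*Protocol article*

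**What the plan says.** All of this comes from the protocol article.

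- **Statistical analyses.** Every primary analysis follows ITT. The section then warns: "There is a risk that not every patient in the IG will have a feedback session during his or her withdrawal treatment". Three possible reasons follow: "This could result from time constraints for the therapists, unscheduled dropouts from treatment, or premature referrals for subsequent treatment". The response is that "additional per-protocol analyses will be conducted that include only those patients who actually participated in the intervention". No rule is given for the CG.
- **Intervention.** "Patients in the CG will not have an additional feedback session regarding their further treatment options and are treated as usual". In the IG, the research assistant first goes through the level-of-care recommendation with the therapist or social worker, and the patient's session comes afterwards.
- **Procedure.** Allocation is disclosed at the end of the baseline interview. After that, "For patients in the IG, the research assistant will schedule the feedback session".
- **Primary outcomes.** There are two: health-care costs, and for drinking "per cent days of heavy drinking in the last 30 days (PDHD) was chosen as the primary outcome measure".

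**The concern.** Attendance at the session is settled after randomization and exists in one arm only. CG patients can also leave the ward unexpectedly or be referred early, but nothing in the stated rule removes them. The two groups being compared therefore no longer have the same expected prognosis, even if the intervention does nothing.

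The analysis is the article's stated answer to incomplete delivery, which is a fair question to ask. The risk is that a per-protocol difference is taken as the effect of the intervention when delivered, although a reader could not separate effect from selection. The covariates named for the arm comparison (baseline costs and PDHD, age, gender, co-morbidity, EQ-5D) need not capture why someone leaves a withdrawal ward early.

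**Working it through.** **The plan's own figure.** 100 analyzable cases per arm with 30% dropout: 100 / (1 − 0.30) = 142.86, rounded up to 143 per arm and 286 in total. This agrees with the Sample-size calculation section and is not affected by the point.

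**Which arm can lose patients.** The session exists only in the IG and is scheduled after allocation is known. Exclusion for non-attendance is therefore impossible in the CG. Taken literally, requiring participation in the intervention leaves no CG patient in the set. The workable reading is IG attenders against the whole CG.

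**Size of the bias under no true effect.** Let q be the IG share excluded and g the mean PDHD of the excluded minus that of the retained. The CG mean is q × (excluded mean) + (1 − q) × (retained mean), and the per-protocol IG mean is the retained mean. The difference, IG minus CG, is −q × g.

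From the article: 100 analyzable cases per arm. Assumed: q, g, SD 35, an unadjusted normal comparison, and the same share excluded among analyzable cases as among those randomized.

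SE = 35 × √(1/(100(1 − q)) + 1/100)

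Two-sided rejection rate at 5% = Φ(|bias|/SE − 1.96) + Φ(−|bias|/SE − 1.96)

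For q = 0.20 and g = 25: bias = −5.0; SE = 35 × √(1/80 + 1/100) = 5.25; ratio 0.952; Φ(−1.008) + Φ(−2.912) = 0.157 + 0.002 = 0.159.

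| q | g (points) | Bias (points) | SE | Two-sided rejection |
|---|---|---|---|---|
| 0.10 | 15 | −1.5 | 5.09 | 6.0% |
| 0.20 | 25 | −5.0 | 5.25 | 15.9% |
| 0.30 | 25 | −7.5 | 5.45 | 28.0% |
| any | 0 | 0 | – | 5% |

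**Direction.** Split the excluded by reason k, with share q_k and deviation d_k from the overall mean. The bias is −Σ q_k d_k / (1 − Σ q_k). Hold total exclusion at 20% and assume dropouts lie 20 points above the mean, early referrals 20 points below it, and time-constraint cases at it. A deviation of 20 from the overall mean is the same as a gap of 25 from the retained, since 0.8 × 25 = 20.

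| Excluded | Bias in PDHD, IG minus CG |
|---|---|
| 20% dropouts | −0.20 × 20 / 0.80 = −5.0 |
| 15% dropouts, 5% referrals | −(3 − 1) / 0.80 = −2.5 |
| 10% dropouts, 10% referrals | 0 |
| 5% dropouts, 15% referrals | −(1 − 3) / 0.80 = +2.5 |
| 20% referrals | +5.0 |
| 20% time constraints | 0 |

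Negative values favour the IG.

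**Costs.** If the excluded 20% are EUR 2000 cheaper than average (assumed), the bias is −0.20 × (−2000) / 0.80 = +EUR 500, against the IG. If they are EUR 2000 dearer, it is −EUR 500, in its favour.

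**The case against.** The strongest reply has four parts.

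1. **ITT governs every primary analysis, and the per-protocol analyses are described as additional.** The trial is called exploratory, and the Discussion says a larger trial will be needed for a more valid estimate. This stands. It confines the point to the supplementary result.

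2. **The direction of bias is not established.** A reader might infer that the per-protocol analysis favours the intervention, and that the article itself ties the reasons for a missed session to prognosis. The documents support neither. The three reasons are given only as reasons for missing the session; nothing is said about their relation to outcome. Therapist time constraints may be neutral, patients referred early may drink less than average, and costs may move the other way. This also stands. It does not rescue the analysis, because a bias of unknown sign still cannot be told apart from an effect.

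3. **The error rates are illustrative.** The share, gap and SD are all assumed, and the model is unadjusted and normal, whereas the article plans adjusted gamma models with a log link. This stands as a limit on the numbers. The mildest scenario, at 6.0%, is close to nominal.

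4. **A CG rule may be in an analysis plan that is not shown.** This is possible, and the absence of such a rule from the article is not the point. The rule that the article does state is attendance at a session that the CG never has, so no CG rule can mirror it. A plan that used a criterion open to both arms would already have changed the analysis.

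**Conclusion.** The point holds for the supplementary per-protocol analysis only. As stated, it conditions on a post-randomization event confined to the IG, so it loses the protection of randomization and is open to selection bias. On heavy drinking the bias favours the IG if unscheduled dropouts predominate among the excluded and can reverse if early referrals do. For costs the sign is unknown.

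At 20% excluded, the PDHD bias runs from −5 through 0 to +5 points across the assumed mixes of reasons. A bias of 5 points in either direction raises the two-sided false-positive rate to about 16% with SD 35. None of the shares, gaps or the SD is in the documents. The structural finding does not depend on them; the size does. The ITT results are untouched.

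**What to change.** **Change.** Replace or accompany the per-protocol contrast with a complier-average causal effect for each primary outcome, using randomized arm as the instrument for receipt and adjusting for site and baseline values. CG patients are not offered the session, so non-receipt is one-sided.

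State the exclusion restriction openly. The recommendation is reviewed with the therapist or social worker before the session, so an IG patient who misses the session may still be affected through the staff. Define receipt as starting at that review, or report both definitions.

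If a restricted-sample analysis is kept, apply one rule to both arms, for example still on the ward at a fixed day after the initial assessment, and label the result non-randomized. That rule is still post-randomization, but it removes the one-sided exclusion.

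**Cost.** Mainly analysis-plan wording. The documentation form captures the session results, sessions are audiotaped, and follow-up is timed from discharge, so discharge dates must be known. Whether the form records that the staff review took place, and not only dissent from the recommendation, should be checked.

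The statistical price is a wider interval: before adjustment the estimate is roughly the ITT difference divided by the share receiving, so at an assumed 80% receipt the interval is about 1/0.80 = 1.25 times as wide as the ITT interval. The estimate also relies on the exclusion restriction, which the data cannot fully verify.

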
The use of matching guidelines in the German SAT has also been the subject of discussion [17]. Recently, our study group conducted two pilot studies on the feasibility of using matching guidelines for patients with alcohol dependence following their participation in an inpatient withdrawal program. *Qualified withdrawal treatment* is a German-specific treatment program that includes, in addition to medically supervised detoxification, several therapeutic components aimed at enhancing patients’ motivation to remain abstinent, and referral for further treatment, if this is indicated [18]. Placement-matching decisions are often made during qualified withdrawal treatment. Our first pilot trial that included 54 alcohol-dependent patients in qualified withdrawal treatment indicated that both the setting and the procedures of the study would be feasible with minor adaptations [19]. In a second preparatory study using Delphi methodology, we asked experts in the German SAT to identify all relevant treatment options for patients with alcohol-use disorders in Germany and to organize them into four LOCs based on current evidence and discussions among the experts [20]. As a result, minor adaptations in the matching guidelines were made (see Figure 1).

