**Adapted allocation guidelines for referral decisions after detoxifications.**

## Methods

### Trial objectives and research questions

The objectives of this study are the evaluation of the matching approach that was previously adapted to include (a) using the MATE as the standardized intake assessment, (b) a treatment recommendation for each patient based on the MATE results, and (c) a feedback session with the patient. Following the recommendations developing and evaluating complex interventions [16], we are combining evaluation of the efficacy of the intervention with a process evaluation [21]. The hypotheses regarding the effects of the matching guidelines on reduction in alcohol consumption and health service costs are as follows:

H1: Patients in the intervention group (IG) will have fewer heavy-drinking days during the 30 days prior to the follow-up interview than those in the control group (CG).

H2: Patients in the IG will have lower health-service costs during the six months after the initial assessment than those in the CG.

The process evaluation will address the following research questions:

R1: How are trial outcomes related to variations in the extent and quality of the implementation of the intervention? We expect differences between study sites due to regional variations of the participating SAT.

R2: What are the factors that mediate the effects of the intervention received on treatment outcome? Mediating variables are expected to occur at the patient level (i.e. motivation, treatment preference, sociodemographic and clinical characteristics), the treatment level (i.e. recommendations that the therapists make, overall treatment effects), and the regional level (i.e. regional variations in the availability of treatment options, whether or not funding agencies approve the treatment). Previous studies regarding placement matching imply that there may be more variables mediating the effect of the intervention than captured in the actual matching algorithm. Due to a lack of evidence for major changes to the algorithm before starting the trial, it was decided to include those variables as possible mediators.

R3: Are there subgroups that differ in their response to the intervention? We expect that patients having specific treatment needs, e.g. pregnant women or patients with severe co-morbid psychiatric or physical disorders, might differ from other patients in their response to the intervention.

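### The gamma model named for both primary outcomes does not admit a value of 0, which percent heavy-drinking days takes in every patient with no heavy-drinking day

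*Protocol article*

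**What the plan says.** Under Primary outcomes, the article states that "The primary outcome measures will be alcohol consumption and health-care costs". For drinking, "per cent days of heavy drinking in the last 30 days (PDHD) was chosen as the primary outcome measure". The matching hypothesis, H1 (Trial objectives and research questions), is that intervention patients "will have fewer heavy-drinking days during the 30 days prior to the follow-up interview" than controls.

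Under Statistical analyses, differences between the arms "regarding the primary outcomes will be analyzed using generalized linear models with gamma distribution and log-link function", controlling for confounders. The examples of confounders include baseline PDHD, so the drinking outcome is clearly in scope. The article's e.g. qualifies only the list of confounders, not the distribution. It continues: "To account for correlated patient data caused by the multicenter structure, random-effect models will be applied". The same section commits all primary analyses to intention to treat.

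The article gives no separate model for PDHD, no two-part or hurdle step, no rule for zeros and no estimation method.

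**The concern.** A gamma model with log link is a usual choice for positive, right-skewed costs. PDHD is a different kind of variable: a count of days out of 30 on a percentage scale, with 31 possible values from 0 to 100. Zero is a result the treatment aims for, since the Background describes withdrawal treatment as meant to strengthen "motivation to remain abstinent". The zeros also include patients who drink without drinking heavily, a wider group than the abstinent.

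PDHD is the only drinking outcome on which H1 is tested. If the named distribution cannot hold the data, the analyst has to choose a way round it after seeing them. The possible choices differ sharply in whom they include and in what P value they give.

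**Working it through.** **The plan's own figure.** Sample-size calculation asks for 100 analysable cases per arm and assumes 30% dropout: 100 / 0.70 = 142.9, rounded up to 143 per arm and 286 in total. This reproduces exactly. It does not depend on the outcome model, so nothing below alters it.

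**Can the gamma likelihood hold a zero?** The gamma log-density contains the term (a − 1) log y, where a is the shape. As y goes to 0:
- a = 0.5: +infinity
- a = 2: −infinity
- a = 1: finite (−log 20 = −3.00 at scale 20)

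Only a shape of exactly 1 gives a finite value, so one zero makes the likelihood unusable. Random-effects models are normally fitted by that likelihood.

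**Can the mean model be fitted without the likelihood?** With gamma variance and log link, the estimating equations are Σ x(y − μ)/μ = 0, which are defined at y = 0. With arm as the only covariate, the fitted means are the arm means. In one simulated data set with zeros, the coefficients came out (log ratio −0.441, ratio 0.64) while the log-likelihood was infinite.

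**Simulation inputs.** The 100 per arm is from the article. The rest is assumed: the shares with 0 heavy-drinking days; a daily probability of Beta(0.8, 1.2) among the others, with days drawn as Binomial(30, p) and a minimum of 1; and arms that differ only in the zero share. The true mean ratio is then (1 − zero share, intervention) / (1 − zero share, control). The number left after dropping zeros is 100 times the sum of the two non-zero shares.

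| Zero share, control / intervention | True ratio | Patients left of 200 | Gamma, positives only: ratio, rejection | Mean ratio, all patients, robust SE: ratio, rejection |
|---|---|---|---|---|
| 30% / 45% | 0.55/0.70 = 0.79 | 70 + 55 = 125 | 1.00, 6% | 0.79, 28% |
| 50% / 65% | 0.35/0.50 = 0.70 | 50 + 35 = 85 | 1.00, 6% | 0.70, 32% |
| 60% / 75% | 0.25/0.40 = 0.63 | 40 + 25 = 65 | 0.99, about 6% | 0.61, 41% |

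At 50% / 65%, a quasi-likelihood gamma/log fit with all zeros kept gave a ratio of 0.70 and 32% rejection. A fractional logit on all patients gave 33%. With equal zero shares in both arms, the quasi-likelihood fit rejected in 4.0% to 5.2% of runs.

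**Replacing zeros by a constant.** In one data set simulated at 50% / 65%, the likelihood-based SE of the log ratio is √((1/a)(2/100)):
- constant 0.01: a = 0.185, SE 0.33, ratio 0.64
- constant 0.1: a = 0.257, SE 0.28, ratio 0.64
- constant 1: a = 0.437, SE 0.21, ratio 0.65

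Over repeated trials at 50% / 65%, the ratio moved only from 0.70 to 0.72. Maximum-likelihood rejection rose from about 9% at 0.01 to about 35% at 1. A separate set of 300 runs gave 18%, 26% and 36% at 0.01, 0.1 and 1. The level at 0.01 differs between the two sets, but both show rejection rising with the constant.

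**The case against.** The strongest reply is that nobody is forced to drop patients. A generalized linear model needs only a mean and a variance function. Fitted by quasi-likelihood, the gamma/log model keeps every zero, recovers the mean ratio, holds its size and nearly matches a fractional logit (32% against 33% rejection). The article names no estimation method, says nowhere that zeros will be excluded, and its intention-to-treat commitment argues against excluding them. The trial is also called exploratory and was not sized on its primary outcomes, and an unseen analysis plan may settle the fitting method.

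Most of this stands. A reader might infer that the analyst must discard patients without heavy drinking, or that an intention-to-treat breach is planned. The article supports neither. The loss of power in the positives-only column belongs to an analysis it does not prescribe. H1 speaks of fewer heavy-drinking days, not of more patients at zero, so the assumption that the whole effect acts through zeros is the case least favourable to that analysis.

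The reply does not remove the stated distribution. The article names a gamma distribution and adds random effects, without mentioning quasi-likelihood or robust variance. The workable route is therefore not the one written down. An analysis plan could supply a fitting method, but the distribution named in the article would still be unsuitable for this outcome. The exploratory label does not help either, because a choice left until the data are seen is open to being driven by results.

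**Conclusion.** The point holds as a misstated model for PDHD. It is not a missing detail, and it does not touch the gamma model for positive costs. A likelihood-based gamma mixed model cannot be fitted as written once any patient has no heavy-drinking day. That conclusion needs no assumption about how many there are.

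The size of the damage depends on the way round that is chosen:
- Quasi-likelihood with zeros kept: essentially none for the arm comparison in the simulations, which had no covariates or site effects.
- Zeros dropped: at worst, a true ratio of 0.70 appears as about 1.0 in 85 of 200 patients, with rejection at the null rate.
- Zeros replaced by a constant: the ratio is almost unchanged, but maximum-likelihood rejection runs from about 9% to about 35%.

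These figures rest on assumed zero shares, since the documents give none, and on an effect acting only through zeros. They illustrate what is at stake and do not forecast this trial's result.

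The cap at 100 is secondary. A log link can give individual fitted values above 100 once covariates enter, but no harm to the arm comparison has been shown.

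**What to change.** Keep the gamma/log-link model for health-care costs. For PDHD, name a separate model of heavy-drinking days out of 30 that includes every analysed patient with zeros kept: a fractional (quasi-binomial) logit with robust standard errors, or a beta-binomial model. Adjust it for baseline PDHD and site, and report the adjusted difference in mean PDHD. Add a hurdle model as a sensitivity analysis. State that no patient is excluded from the H1 analysis because the outcome is 0 and that no constant is added.

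The model should be fixed before outcome data are compared by arm. The change is to wording only: it needs no new data or patients, and the planned 286 is unaffected.

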In order to implement patient-treatment matching in routine care, matching guidelines have been developed and evaluated in several countries. The guidelines usually define a set of criteria that can be used to determine an appropriate treatment or level of care (LOC) for each patient. In the United States, the Patient Placement Criteria of the American Society of Addiction Medicine are the most frequently used and evaluated placement criteria [4,8,9]. Recently, in the Netherlands matching guidelines were developed, evaluated, and implemented in the context of a nationwide reorganization of the SAT [10-12]. This approach was based on existing evidence on the efficacy of placement matching; it combines the concept of stepped care with the matching of treatment services according to patients’ needs [11,12]. Depending on their history of substance abuse treatment and their degree of impairment along the dimensions of *addiction severity*, *psychiatric impairment*, and *social instability*, patients can be assigned to brief outpatient treatment (LOC1), outpatient treatment (LOC2), day/residential treatment (LOC3), or inpatient or outpatient long-term care (LOC4; [11]). *Measurements in the Addictions for Triage and Evaluation* (MATE) [13] is the assessment instrument that was developed to implement these guidelines. The MATE is feasible for use in routine care, and it provides all of the information necessary to arrive at a recommendation of one of four LOCs according to the matching guidelines [14]. Studies on the feasibility and predictive validity of the Dutch guidelines have shown promising but inconclusive results. That is, the guidelines have been implemented successfully and have been shown to be feasible to use in routine care [11], but there was no effect on drinking outcome at a nine-month follow-up assessment. The authors, therefore, recently concluded that the matching guidelines need to be revised [15]. By now, necessary revisions are still being discussed in the Netherlands. It should be recognized, however, that various complexities are involved in using matching guidelines and various factors affect how effective using them is. This includes the structure of the particular SAT service in which they are used, the number of agents involved in the decision-making process (e.g. patients, therapists, treatment centres, funding agencies), and regional variations in the availability of treatment options. It is therefore appropriate to evaluate matching guidelines according to the guidance for the development and evaluation of complex interventions [16].

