### Sample-size calculation

Due to the exploratory nature of the trial, the sample-size calculation was based on considerations regarding the process evaluation rather than the primary outcome measures. The concordance between MATE recommendations and actual referrals to the recommended LOC was considered to be an important mediator between the intervention and the outcome measures. Because classification into concordant (matched) and discordant (mismatched) decisions yields a cross-classification in addition to the LOC groups and study arms, it was important to ensure that in both study arms all of the cells include at least 10 analyzable cases at the six-month follow-up. Based on prior studies [11,19], we expected an imbalance between the four LOCs (approximate ratio: 1:3:5:1). Based on these assumptions, 100 analyzable cases would be needed in each arm at follow-up. Assuming a drop-out rate of 30 % between randomization and follow-up, 143 patients should initially be included in each study arm (or 286 patients in total). This sample size would ensure that subgroup analyses can be conducted, even if attrition rates are higher than expected or they differ among study arms or LOCs. Figure 3 shows the expected flow of patients.

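### The single mismatched category pools a higher level of care, a lower level and no further treatment, so its coefficient, above all for costs, depends on an unreported mix of directions

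*Protocol article*

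**What the plan says.** The Protocol article, under Statistical analyses, states that "patients who received treatment according to MATE guidelines will be designated matched", and that "those who did not will be designated as mismatched". The status of the analysis is given as follows: "Subgroup analyses will include effects of the classification as matched vs. mismatched decisions for patients in both the IG and the CG". The model is also fixed: "The effect of matching MATE recommendations with treatment received on the primary outcome measures will be analyzed using multiple linear regressions". Under Primary outcomes these measures are the percentage of heavy-drinking days (PDHD) and health-care costs, the latter being service use from the CSSRI-EU valued at unit costs.

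Under Sample-size calculation, concordance "was considered to be an important mediator between the intervention and the outcome measures", and the cell counts rest on a "classification into concordant (matched) and discordant (mismatched) decisions", crossed with LOC and study arm.

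The Background section lists the levels: "patients can be assigned to brief outpatient treatment (LOC1), outpatient treatment (LOC2), day/residential treatment (LOC3), or inpatient or outpatient long-term care (LOC4"). MATE recommends one of these four for each patient. The Statistical analyses section also plans to examine therapists' reasons for deviating from the recommendation. Nowhere are drinking or costs analysed by the direction of the mismatch.

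**The concern.** MATE always points to one of four levels. A patient recommended LOC2 who enters LOC3, a patient recommended LOC3 who enters LOC2, and a patient recommended LOC3 who receives nothing after discharge therefore all carry the same code. The regression coefficient for mismatched is an average over these three kinds of patient, weighted by how often each happens to occur.

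That mix is unlikely to be constant. Research question R1 expects site differences because regional services differ. Only the intervention arm is told the recommendation, so the mix may differ by arm. It is also tied to the recommended LOC: a patient recommended LOC1 cannot go to a lower LOC, and one recommended LOC4 cannot go to a higher one. Since the recommendation is built from the MATE severity, social and treatment-history dimensions, direction of mismatch is partly bound up with baseline status.

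At stake is the reading of a process-evaluation analysis that the article treats as important enough to base its sample size on. For costs the difficulty is nearly built in, because the follow-on care that makes a patient mismatched is also counted in the cost.

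**Working it through.** **1. The plan's own figure.** The expected LOC ratio is 1:3:5:1, so the smallest LOC holds 1/10 of patients. Ten cases there need 10 / 0.1 = 100 analysable patients per arm. With 30% drop-out, 100 / 0.7 = 142.9, so 143 per arm and 286 in total, as stated. The calculations below use 200 analysable patients, both arms together.

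**2. What the pooled coefficient estimates.** Let s be the share of mismatched patients who received a higher LOC, a the effect of a higher LOC versus matched, and b the effect of a lower LOC or no care versus matched (merged here only to keep the illustration simple). Then

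pooled contrast = s·a + (1 − s)·b.

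The documents give neither s, a nor b, so all values below are assumptions.

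**3. Costs.** Take a = +4,000 and b = −2,000 euros, so that pooled = 6,000·s − 2,000.

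| s | Pooled cost contrast (euros) |
|---|---|
| 0.10 | −1,400 |
| 0.30 | −200 |
| 0.50 | +1,000 |

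The sign changes at s = 1/3. The amounts are invented. The opposite signs are plausible for costs because treatment received enters the outcome directly.

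**4. Drinking.** Take b = +0.4 SD (worse) and vary a. Entries are the pooled contrast in SD units, with power for 100 matched versus 100 mismatched in brackets.

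| a | s = 0.10 | s = 0.25 | s = 0.50 | s = 0.75 |
|---|---|---|---|---|
| −0.4 (opposite) | 0.32 (62%) | 0.20 (29%) | 0.00 (error rate only) | −0.20 (29%) |
| 0 (no effect) | 0.36 (72%) | 0.30 (56%) | 0.20 (29%) | 0.10 (11%) |
| +0.4 (same) | 0.40 (81%) | 0.40 (81%) | 0.40 (81%) | 0.40 (81%) |

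Full cancellation needs opposite signs and one particular mix. With no effect in one direction there is dilution. With equal effects nothing is lost.

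**5. Price of separating the directions.** The standard error of a difference in means, in SD units and without covariates, is sqrt(1/n1 + 1/n2).

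- Half mismatched, split 70 lower-or-none and 30 higher:
  - pooled sqrt(1/100 + 1/100) = 0.141
  - lower-or-none sqrt(1/100 + 1/70) = 0.156
  - higher sqrt(1/100 + 1/30) = 0.208
- 70% matched and only 6 of 200 at a higher LOC:
  - pooled sqrt(1/140 + 1/60) = 0.154
  - higher sqrt(1/140 + 1/6) = 0.417

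Adjusting for recommended LOC will change these somewhat.

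**6. How fine the split can go.** Ten cases in every combination of LOC and matched/higher/lower-or-none would need, with 50% matched and an even split of directions, 10 / (0.1 × 0.25) = 400 per arm against 100 planned. The direction contrasts therefore have to be pooled over LOC and arm, with LOC as a covariate.

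**The case against.** Several points on the other side are sound.

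- **Limited reach.** H1 and H2 are intention-to-treat comparisons of the arms and do not use this classification. The trial is declared exploratory, and the Discussion says a larger trial will be needed for more valid and reliable effect estimates.
- **Cancellation is not shown.** A reader might infer that opposite effects cancel and leave the matching question without an interpretable answer. The documents do not support that, because they give no mix and no effect by direction. If the best-fitting treatment is what helps, both directions could worsen drinking and pooling would cost nothing. The pooled contrast still describes following versus not following the recommendation, averaged over the mix observed.
- **Revising the algorithm.** A reader might also infer that pooling defeats the plan to decide whether the algorithm needs changing. The article bases that decision on therapists' documented reasons for deviating, not on this coefficient.
- **The levels are not a clean ladder.** LOC4 is long-term care, inpatient or outpatient, and differs in kind. A move from LOC3 to LOC4 is not plainly a step up in intensity.
- **Partial recovery through LOC.** The sample-size section crosses matching with LOC, which reveals part of the direction in LOC1 and LOC4. It does not do so in LOC2 and LOC3, which hold 8 of every 10 patients under the expected ratio and where mismatch can go either way.

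It can also be said that an analysis plan could add a finer split. But the article itself fixes the two-level definition, the model and the dependent variables, so this is a stated choice rather than an omitted detail. These objections narrow the point. They do not remove it for costs.

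**Conclusion.** The point holds in a limited form. The two-level code pools a higher LOC, a lower LOC and no further treatment, and no analysis of either primary outcome separates them.

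For costs, the coefficient largely reflects the mix of directions and could take either sign: under the assumed amounts it runs from −1,400 to +1,000 euros as the upward share goes from 10% to 50%. For drinking, dilution or masking arises only if the directions differ in effect, which is an assumption. Under the scenarios shown, a 0.40 SD effect of less or no care may appear as anything from 0.40 to −0.20 SD.

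The stronger conclusion that the pooled coefficient should not be interpreted at all does not follow: it remains a legitimate average. The primary comparisons are unaffected. This is a worthwhile, inexpensive improvement to a secondary analysis, not a flaw in the trial's main test.

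**What to change.** Keep the matched versus mismatched contrast, described as the average effect of not following the recommendation over the observed mix. Add to the planned regressions, for both PDHD and costs and adjusted for recommended LOC, three contrasts against matched:

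1. higher LOC than recommended;
2. lower LOC than recommended;
3. no further treatment.

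Merge (2) and (3) only if counts are too small. Report mismatches into or out of LOC4 separately, since they are not cleanly ordered. Tabulate counts by direction, arm and site, and draw conclusions about costs from the direction-specific contrasts. Where a category is sparse, describe it without estimating an effect.

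No new data are needed. All patients have a MATE, which calculates the recommended LOC automatically; referral decisions are documented in both arms; and service use is collected at follow-up. The cost is some added wording in the analysis plan and wider intervals: about 0.16 and 0.21 SD against 0.14 SD pooled in the 100/70/30 split, and about 0.42 SD for the higher-LOC contrast if only 6 of 200 patients fall there.
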